**Figure 1 figure1:**
[figure not shown]
Design of ATN Protocol 148—randomized controlled trial for youth living with HIV (YLH). AMMI: automated messaging and monitoring intervention.

As part of the voluntary informed consent procedures, YHL are asked to provide additional consent to access sensitive information for care coordination and study retention (locating missing participants) for the duration of the study (24 months), which includes their contact information; social media accounts; contact information of their close relatives, friends, and providers including case managers and probation officers; social security number; driver’s license or identification card number; and access to their medical records. Providing this additional information is not mandatory, and YLH can refuse to provide these permissions as long as they provide their own contact information; all information will be stored securely in the CommCare system. Only the study team will have access to this information.

### Assessments

Following enrollment, study participants will be asked to complete a baseline assessment, which is administered by the interviewer using Android tablets in approximately 45 minutes. This assessment covers the following sections: background, risk behaviors, and sociodemographic variables as well as eight cross-cutting domains related to the HIV Treatment Continuum [12]. Interviewers enter the participants’ responses in the CommCare system developed by the Dimagi Corporation, Cambridge, MA. CommCare is an open-source, mobile phone-based platform that is cloud based and HIPAA (Health Insurance Portability and Accountability Act) 1996 compliant. This mobile app is used to collect all study data and send out short message service (SMS) messages and weekly surveys as part of AMMI as well as spontaneous broadcast messages for particular groups of participants.

Participants also have a blood draw for viral load monitoring and a series of rapid diagnostic tests (RDTs) which include the following:

HIV as part of screening: Potential study participants undergo HIV testing using the CLIA-waived Alere (Waltham, MA) Determine HIV-1/2 Ag/Ab Combo finger stick blood test for both HIV-1/2 antibodies and the HIV-1 p24 antigen with a window period of 12-26 days, which can be read in 20-30 minutes. Once enrolled in the study, participants also receive HIV testing using the Cepheid (Sunnyvale, CA) Xpert HIV-1 Qual Assay, which is highly sensitive, uses whole blood to detect HIV-1 total nucleic acids, and has a 92-minute read time.Chlamydia and Gonorrhea are tested using a Food and Drug Administration-approved Cepheid Xpert CT/NG Assay polymerase chain reaction that is read in 90 minutes.Syphilis is tested using the CLIA-waived Syphilis Health Check finger stick blood test to detect treponemal antibodies with a 10- to 15-minute read time.Hepatitis C is tested using the CLIA-waived OraQuick HCV Rapid Antibody test finger stick blood test with a 20- to 40-minute read time.Substance use is tested using a multidrug urine test panel to detect the presence of marijuana, cocaine, opiates, and methamphetamine with a 2- to 5-minute read time.Alcohol use is assessed using a breathalyzer test that is sensitive for assessing alcohol use in the last 24 hours.

Following completion of the baseline assessment, participants will receive a US $50 cash incentive. Any study participant who tests positive for HIV or a sexually transmitted infection (STI) will be offered immediate access to treatment.

### Follow-Up Assessments

Study participants will be reassessed every 4 months over a period of 24 months. In total, the study participants will complete six follow-up assessments and receive a US $50 cash incentive for each follow-up assessment. Follow-up assessments will include another 45-minute assessment, a blood draw for viral load monitoring, and a series of RDTs for STIs and substance use, as described above. In addition, if study participants report any potential STI symptoms or exposure, they will immediately be offered testing. In between assessments, YLH who need STI testing can use standard care in the community or contact the study team for assistance. At these assessments, participants who are not virally suppressed (viral load<200 copies/mL) will “step up” to the next level of care while still receiving the prior level(s) of care.

### Outcome Measures

#### Primary Outcome: HIV Viral load

The primary outcome measure is a suppressed viral load at each 4-month assessment for 24 months. At both sites, whole blood is collected with the anticoagulant EDTA and sent at ambient temperature to an internal laboratory where plasma is separated. In addition, 1.5-3.0 mL plasma is shipped to an off-site CLIA-certified laboratory to measure viral load by quantitative HIV-1 RNA real time polymerase chain reaction with a level of detection of 20 copies/mL. Samples from New Orleans are measured at room temperature and those from Los Angeles are measured after they are frozen and thawed. The study team will receive the results through the laboratory’s online portal.

#### Secondary Outcomes

The following secondary outcomes are also measured at each 4-month assessment for 24 months.

##### Retention in Care

YLH are deemed to be retained in care if they attend at least two medical appointments annually. When starting ART, three appointments are scheduled in the first 3 months. Therefore, retention in care also depends on how long YLH have been prescribed ART. We will assess YLH every 4 months; therefore, there are six opportunities over the 24 months of follow-up to obtain self-reports during medical appointments and ensure adherence to ART regimens.

##### Antiretroviral Therapy Adherence

ART adherence is based on a Likert scale that asks YLH to rate their ability to take all their HIV medications as prescribed over the prior 30 days. Response categories range from “Very poor” (1) to “Excellent” (6) [72,73].

##### Alcohol Use Over the Past 4 Months

This parameter will be assessed using the Alcohol Use Disorders Identification Test, consisting of three questions with Likert-scale responses [74].

##### Substance Use

YLH will be asked to indicate if they used any of the following substances over the past 4 months: marijuana, synthetic marijuana, cocaine or crack, heroin, ecstasy, methamphetamines, prescription stimulants or amphetamines, gamma hydroxybutyric acid, ketamine, poppers, inhalants, hallucinogens, prescription painkillers not used as prescribed, and other prescription medications not used as prescribed. YLH will also be asked how many times they injected “drugs such as heroin, opiates, cocaine or amphetamines (crystal)” over the past 4 months. RDTs for alcohol and substance use will be administered to evaluate the degree of underreporting when RDTs indicate use but self-reports do not. Given the fairly short window of detection for RDTs (eg, 24 hours for alcohol), RDTs are not used as outcomes.

##### Sexual Behavior

YLH will be asked to report on the following sexual behaviors over the past 4 months: the number of sexual partners (in total and partners who are HIV positive) and the number of insertive and receptive anal sex acts. YLH will also be asked the frequency of condom use with sexual partners at each sexual encounter. Responses categories range from “None of the time” (0) to “All of the time” (5).

##### Mental Health

Mental health is assessed using three scales. YLH will be administered four questions from the 12-item Short Form Health Survey [75]. Specifically, they will be asked if they “felt calm and peaceful,” had “a lot of energy,” and “felt sad and blue” during the past 4 weeks. Response categories range from “None of the time” (0) to “All of the time” (5). YLH are administered the Patient Health Questionnaire for adolescents (PHQ-A) [76], which asks YLH to report how often they were bothered by problems from a list of nine items over the past 2 weeks. Lastly, YLH are administered the Generalized Anxiety Disorder 7-item scale [77]. Similar to the PHQ-A, YLH are asked to report how often they were bothered by problems from a list of seven items over the past 2 weeks, such as “Feeling nervous, anxious or on edge.”

SMS weekly surveys consist of six items that inquire about how many days YLH felt “sad or depressed;” if they had “any genital itching/pain/discharge, burning during urination, lower stomach pain, or discomfort during sex;” how many times they had sex without using a condom; how many days they used “alcohol and/or drugs;” how many days they did not have a place to sleep; and how many days they missed taking medications. Surveys mainly serve as a tool for research staff to monitor YLH health; check in with them, if needed; and encourage YLH to self-monitor their health and behavior. Items for medication adherence, alcohol/substance use, and sadness/depression will also be treated as outcomes in analyses similar to secondary-outcome analyses. However, low SMS survey–response rates are anticipated based on prior studies with YLH [78]. Therefore, analyses on SMS survey outcomes will be treated as exploratory; precedence will be given to analysis results for secondary outcomes from the 4-month assessment.

##### Costing

Costs are of two types: costs of delivering the intervention and additional costs incurred by participants for their use of health care services and services from other agencies. The cost of delivering the intervention requires an estimation of staff time. Coaching logs and other intervention information will be entered into CommCare, which does not provide information regarding the amount of time spent performing study tasks. Thus, staff activity information that is captured by this system will be supplemented by *Time It*, a mobile app that allows individuals to record the time spent carrying out different staff activities [79]. Each staff member, including program directors, interviewers, and coaches, will record relevant categories of activity over the course of 1 week per quarter. A set of staff activity categories will be prespecified in the mobile app. However, staff are allowed to add more categories as they perform other tasks not previously specified. In addition, personnel time will be estimated from several sources; budgeted time and time recorded on time sheets, for hourly employees, will provide a basis for each staff member’s hours devoted to the project.

The costs of additional services are derived from respondent reports of utilization and medical records and will be estimated using publicly available data. Research-specific costs (eg, incentive payments, informed consent, screens, and software adaptation for survey tools) are excluded from the total costs. All cost data will be adjusted for price back to Year 1 of the study by using the medical care component of the consumer price index.

### Description of the Intervention

As shown in Figure 1, the Enhanced Stepped Care condition has three levels of intervention: Level 1, Enhanced Standard Care plus AMMI; Level 2, online peer support via social media plus AMMI plus Enhanced Standard Care; and Level 3, coaching plus online peer support via social media and AMMI plus Enhanced Standard Care. If YLH fail to be virally suppressed (based on analyses of viral load in the blood stream at 4-month intervals), YLH in the Enhanced Stepped Care condition will be provided the next level of intervention in addition to the other levels of care to which they were previously assigned. Note that these interventions overlap with our team’s other study of HIV-negative youths and are also described in Swendeman et al [49]. To assess dose of the interventions, we will examine the number of responses to the AMMI surveys (Level 1), the number of peer support posts and logins (Level 2), and the number of coaching sessions (Level 3).

#### Level 1

Level 1 of the Enhanced Stepped Care model is Enhanced Care plus AMMI. As this is not a medication treatment study, YLH are treated in the community using best practices that are consistent with available treatment guidelines for providers. However, given that YLH have failed to achieve viral suppression with the existing services available to them, we are enhancing standard care by adding an additional component. Thus, Enhanced Care includes existing services received by YHL from health care providers and other agencies as well as daily text messages. Messages for this study focus on five areas: wellness, health care, medication reminders, drug use, and sexual health. We have tailored and adapted preexisting libraries of theoretically based text messages that have been found to be successful in other RCTs with similar populations [80-83], with messages tailored for two different groups—GBTY and non-GBTY. Messages include a focus on empowering YLH (ie, “Don't rely on other people, take your health seriously,” and “When you take your meds regularly, you’re in control”) as well as providing health-related facts (“Meds keep HIV in check” and “Syphilis can increase your viral load”). The goal of AMMI is to target the areas that can impact adherence to ART that will translate into increased rates of viral suppression.

#### Level 2

The second level of our Enhanced Stepped Care intervention is a secure, private online/social media peer-support intervention. Participants are invited to participate in an online discussion board through muut.com, an open-source discussion forum that is mobile and desktop friendly. Project staff review access requests to ensure that only participants are attempting to join the board. YLH can personalize their Muut profiles using avatars and (nonidentifying) photos, but cannot choose usernames that compromise their anonymity. Online discussion boards are tailored to topics relevant to youth. Others’ experiences with interpersonal group interventions for high-risk youth indicate that group cohesion based on these factors can be a key factor influencing group participation and retention [84,85]. Discussions can be initiated by youth or study team members, including HIV-specific topics related to linkage and retention in care as well as other challenges experienced by YLH.

On all discussion boards, study team members have administrator privileges, allowing them to monitor all activities, post information for discussion, and credit incentives for participants. They take multiple steps to safeguard confidentiality and continually review online postings and delete any identifying information posted. Users are removed from the discussion boards if they post inappropriate content three times after receiving feedback for each occurrence, which includes solicitation for sex and drug use; racist, homophobic, or other stigmatizing content; pornographic content; or “trolling” inflammatory remarks or personal insults.

#### Level 3

Participants who fail to achieve viral suppression at levels 1 or 2 of the intervention will be assigned to our coaching intervention. Coaching will focus on a variety of risk factors concurrently, as is common in HIV research [86-88], and build on our prior work with this type of intervention. Coaching is based on the strength-based model [89,90] that has demonstrated positive impacts on persons living with HIV [91,92] and HIV prevention [93,94]. Identifying and accomplishing goals are critical components of the model. Sessions can be conducted via phone or in person. At the first session, the coach and youth complete a strength assessment that will addresses six main life domains: daily living (survival needs such as food, housing, finances, and employment), physical health (non-HIV-related health problems), health services and health care related to HIV (insurance, linkage to care, ART adherence, viral suppression, treatment cascade, and adherence), social relationships (social support, disclosure, and stigma), mental health (eg, depression, anxiety, and coping), and risks (substance use and risky sexual behaviors). This assessment is used to guide the development of up to three personalized goals with shared responsibility between the youth and coach, depending on the nature of the goals.

After the assessment, sessions will focus on goal attainment. At each session, the coaches use the skills common to 80% of all child and adolescent evidence-based interventions (EBIs) [95,96]: relaxation, relapse prevention, positive activities/alternatives, referrals, modeling/role playing, positive self-talk, triggers, emotional regulation, monitoring/self-monitoring, support networking/building social support, assertive communication, setting up rewards, problem solving, goal setting, praise, and engagement/rapport building. The use of these skills and their relevance to our coaching intervention are described in further detail in Swendeman et al [49]. The coaching intervention is not manualized but rather relies on the strength assessment, goal setting, and the use of evidence-based skills to develop a personalized plan of intervention for each youth that addresses the unique factors that impact adherence and ultimately, viral suppression. Participation in coaching will continue while the YLH is in the study, but we expect that coaching sessions will decrease in frequency over time as the goals are accomplished.

### Selection and Training Coaches

Our coaching model uses paraprofessionals who have experience and skills in working with the population but do not have advanced degrees [97]. These community members have expertise in addressing the “predictable problems” [98] that these youth experience and will use evidence-based practices to intervene and address specific identified goals [97]. Coaches are also hired based on their interpersonal skills, ability to connect with YLH, and skills in implementing an evidence-based but nonmanualized intervention. They receive intensive training prior to field work to participate in ongoing weekly supervision and have access to real-time supervision in the field.

### Data Analyses

#### Aim 1

Intent-to-treat analyses will be used to compare viral suppression as our primary outcome and secondary outcomes between YLH randomized to the Enhanced Stepped Care or Enhanced Standard Care conditions. Comparisons of the same outcomes will also be made between steps in the Enhanced Stepped Care condition as exploratory analyses; the study is only powered for comparisons between study arms. Multilevel models (MLM [99]) will be used to model correlations between repeated observations on the same YLH in order to properly estimate standard errors. Generalized linear MLM will be fit to discrete outcomes such as the binary outcome for viral suppression. MLM fit to the primary outcome for viral suppression will be parameterized to test for the average of viral suppression differences over the follow-up period between study arms (ie, time-averaged effects). This parameterization will be used because all participants are virally unsuppressed at baseline based on eligibility criteria. Secondary outcome levels can differ across study arms; a more standard parameterization that allows for baseline and slope differences over time will be used. We anticipate that randomization will balance out sociodemographic and other important background characteristics across study arms. If characteristics are found to differ across study arms, they will be included as adjustment covariates in MLM. More sophisticated adjustment methods such as propensity scores will be implemented as needed [100]. Data will also be checked for missing data patterns. Appropriate statistical techniques such as multiple imputation will be applied [98,101].

#### Aim 2

We will use bivariate-outcome MLM to examine temporal relationships between primary and secondary outcomes. Model parameterization will be based on a number of factors, including visualizations of outcome trajectories and model fit statistics. One parameterization that may be used in a bivariate-outcome MLM is a bivariate random intercept and slope model that we have used in a prior HIV study to examine the time-varying relationship between HIV-transmission behaviors and mental health symptoms [102]. This model is formulated through two separate MLM equations for each outcome that is linked through random effects to model random intercepts and slopes. A variance-covariance matrix is modeled to estimate correlations between random effects. Correlations capture time-varying associations between outcomes such as the correlation between the first outcome at baseline and the second outcome over time and vice versa. The bivariate-outcome model offers a flexible modeling framework to test different mediational models. For example, if the bivariate-outcome model contains outcomes for viral suppression, a secondary outcome such as mental health symptoms, and an intervention effect covariate, then we can test if mental health symptoms mediate the impact of the intervention on viral suppression. Details on bivariate random intercept and slope models and other model parameterizations to test for mediational effects in longitudinal data are provided in a previous study [103].

#### Aim 3

Cost-effectiveness analyses will be conducted to weigh the benefit of intervention effects on primary and secondary outcomes against intervention implementation costs beyond those incurred through the standard of care. Specifically, analyses will compare the additional cost required, on an average, to obtain an additional unit of outcome in the Enhanced Stepped Care intervention by calculating the cost effectiveness ratio (CER) [104]. The CER is the difference in total costs of providing an Enhanced Stepped Care intervention versus Enhanced Standard Care, divided by the difference in outcomes of Enhanced Stepped and Enhanced Standard Care [104,105]. The primary outcome of viral suppression and secondary outcomes are outcomes of interest. CER is calculated for different combinations of YLH and provider characteristics. We will conduct sensitivity analyses, as recommended by Gold et al [104], to estimate the extent to which the CER calculation is affected by differences in assumptions about the size of the differences in treatment effect. In particular, we will determine how sensitive the CER is to assumptions that the difference in treatment effect is 1 SD below or above the mean estimated effect size. Similarly, we estimate the sensitivity of conclusions to costs that are 1 SD below or above the estimated mean.

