**Methods:**

YLH (N=220) who are not virally suppressed will be identified at homeless shelters, health clinics, and gay-identified community-based organizations in Los Angeles, CA, and New Orleans, LA. Informed consent will be obtained from all participants. YLH will be randomly assigned to one of two study conditions: Enhanced Standard Care, which includes standard clinical care plus an automated messaging and monitoring intervention (AMMI), or an Enhanced Stepped Care, which includes three levels of intervention (AMMI, Peer Support via social media plus AMMI, or Coaching plus Peer Support and AMMI). The primary outcome is viral suppression of HIV, and YLH will be assessed at 4-month intervals for 24 months. For the Enhanced Stepped Care intervention group, those who do not achieve viral suppression (via blood draw, viral load<200 copies/mL) at any 4-month assessment will “step up” to the next level of intervention. Secondary outcomes will be retention in care, antiretroviral therapy adherence, alcohol use, substance use, sexual behavior, and mental health symptoms.

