#### Sample Size Calculations

Sample size calculations are estimated for our primary analysis, which is a comparison of the probability of viral suppression between Enhanced Stepped and Enhanced Standard Care conditions over five time points. The first follow-up is not included in the comparisons because we anticipate that it will take 6 months for improvements in viral suppression to be seen in the Enhanced Stepped Care condition. Based on our proposed sample size of 220 (n=110 in each condition), we anticipate 80% power for a two-sided test with a .05 alpha level to detect time-averaged percentage differences in viral suppression as small as 9%-13% between conditions. Based on consultation with HIV clinicians, we expect viral suppression rates to be fairly low in the Enhanced Standard Care condition, and we will use a range of rates from 6% to 20% in our calculations. Calculations assume a compound symmetry covariance structure. An autocorrelation coefficient is specified to account for correlations between repeated measurements. Calculations are conducted with a range of autocorrelation coefficient values similar to what we have found in prior studies, from .1 to .3. Lastly, we make a conservative assumption of 20% loss to follow-up so that the sample size in each condition is 88. In practice, we anticipate a much lower attrition rate. Sample size calculations were carried out using Power Analysis and Sample Size software, version 08.0.11 (Englewood, NJ) [106].

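### The exploratory between-step comparison in the Stepped Care arm is confounded by prior outcome, and the article states no adjustment for visit or suppression history

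*Protocol article*

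**What the plan says.** The Data Analyses section (Aim 1) sets out the randomised comparison and then adds: "Comparisons of the same outcomes will also be made between steps in the Enhanced Stepped Care condition as exploratory analyses". The caveat attached is that "the study is only powered for comparisons between study arms".

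The step is not randomised. The abstract's Methods paragraph says that in the stepped arm "those who do not achieve viral suppression (via blood draw, viral load<200 copies/mL) at any 4-month assessment" move up a level. The Description of the Intervention says that on failure "YLH in the Enhanced Stepped Care condition will be provided the next level of intervention in addition to the other levels of care" they already have, and for coaching that "Participants who fail to achieve viral suppression at levels 1 or 2 of the intervention will be assigned to our coaching intervention". No step-down is described.

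On modelling, Aim 1 says "Multilevel models (MLM [99]) will be used to model correlations between repeated observations on the same YLH", with the stated purpose of correct standard errors, and a generalized linear version for binary suppression. Covariate adjustment, with propensity scores as needed, is discussed for characteristics that differ across study arms. Nothing comparable is stated for differences between steps. Sample Size Calculations leaves the first follow-up out of the primary comparison, assumes compound symmetry, and uses a "range of autocorrelation coefficient values similar to what we have found in prior studies, from .1 to .3".

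**The concern.** From month 8 onward, Level 1 holds only participants who have suppressed at every earlier follow-up visit, and Level 3 holds only those who have failed at least twice. Suppression is correlated within a person, so these groups will tend to differ later whatever peer support or coaching achieves. Calling the comparison exploratory and underpowered warns about imprecision. It does not warn that the groups were sorted on the outcome.

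The article's rationale is to give each young person the least intervention needed, so readers will look to step results for evidence on individual levels. An unadjusted contrast could wrongly discredit, or under other choices wrongly credit, peer support and coaching.

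**Working it through.** **Inputs.** From Sample Size Calculations: 110 per arm, 88 after 20% loss; five visits in the primary comparison; control suppression 6% to 20%; compound symmetry with correlation ρ of .1 to .3; two-sided .05; 80% power; detectable difference 9%-13%. From the intervention and follow-up sections: six visits at months 4 to 24, everyone in the stepped arm starting at Level 1, one level up per failed visit, no step-down.

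**The plan's own figure.** Effective n per arm = 88 × 5 / (1 + 4ρ).
- ρ = .3: 440 / 2.2 = 200. The difference detectable with 80% power is 8.5 points from a 6% control rate and 12.3 points from 20%; with a continuity correction, 9.2 and 12.9.
- ρ = .1: 440 / 1.4 = 314. The differences are 6.5 and 9.6 points.

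So 9%-13% is reproduced at the ρ = .3 end. It is a between-arm figure; the article gives none for steps.

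**Month 8, same-visit comparison, levels inert.** Let the rate p be constant and visits exchangeable. Level 1 at month 8 is everyone suppressed at month 4; Level 2 is everyone not.
- P(suppressed at 8 | suppressed at 4) = p + ρ(1 − p)
- P(suppressed at 8 | not suppressed at 4) = p(1 − ρ)
- Difference = p + ρ − ρp − p + ρp = ρ

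| p | ρ | Level 1 | Level 2 | Gap (points) |
|---|---|---|---|---|
| 6% | .1 | 15.4% | 5.4% | 10 |
| 6% | .3 | 34.2% | 4.2% | 30 |
| 13% | .3 | 39.1% | 9.1% | 30 |
| 20% | .1 | 28.0% | 18.0% | 10 |
| 20% | .3 | 44.0% | 14.0% | 30 |

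With 88 in the arm, Level 1 at month 8 would hold only 88 × .06 = 5.3 to 88 × .20 = 17.6 participants.

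**Pooled visits, levels inert.** All 64 six-visit patterns were enumerated under the step-up rule, with beta-binomial correlation (an assumed mixing distribution). Suppression at Levels 1/2/3:

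| p | ρ | Months 8-24 | All visits |
|---|---|---|---|
| 6% | .1 | 17.0 / 6.7 / 5.6% | 6.7 / 6.7 / 5.6% |
| 13% | .1 | 23.9 / 14.4 / 12.0% | 14.6 / 14.4 / 12.0% |
| 13% | .3 | 48.4 / 16.7 / 9.5% | 19.8 / 16.7 / 9.5% |
| 20% | .3 | 53.5 / 24.5 / 14.4% | 29.5 / 24.5 / 14.4% |

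The artefact ranges from very large to almost nil according to which visits are pooled.

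**Multilevel model, levels inert.** A random-intercept logistic model was fitted with level as a time-varying covariate.
- All six visits, correctly specified: level log odds ratios 0.00. Level depends only on outcomes already in the likelihood.
- Month 4 dropped: −0.36 to −1.18 for Level 2 and −0.41 to −1.32 for Level 3. The outcome that set the first step is no longer in the model.
- All visits, but the true correlation serial: −0.07 to −0.37.

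**Sign.** Assume background suppression rises from 6% at month 4 to 20% at month 24, with ρ = .1 and inert levels. Pooling all visits without time gives 7.0/11.1/15.8%, so higher levels look better. The random-intercept model without time gives +0.53 and +1.23; with visit effects, 0.00.

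**The case against.** The strongest reply is that Aim 1 names generalized linear multilevel models in the same paragraph, and that such a model, correctly specified with every visit kept, shows no bias under the null. The month-4 omission is stated for the primary comparison and nothing extends it to the step analysis. The comparison is exploratory, and model detail for an exploratory contrast is normally left to an analysis plan.

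Much of this stands. A reader might infer that the comparison is biased by construction and is bound to show the intensive levels doing worse. The document does not support either statement. The bias can be modelled away, and its direction is settled only for same-visit comparisons with positive within-person correlation. It can reverse when time is ignored. It also reverses in a before-after contrast of those stepping up at month 4: they are at 0% by selection and at p(1 − ρ) at month 8, which for p = 13% is 9.1% (ρ = .3) or 11.7% (ρ = .1) with no effect at all.

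A reader might also extend the criticism to the dose counts, "the number of peer support posts and logins (Level 2), and the number of coaching sessions (Level 3"). The article only says these will be examined to assess dose; it plans no analysis of outcome on dose.

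What does not stand is that the matter is merely missing detail. The article commits to the comparison, gives power as the only caution, justifies the multilevel model by its standard errors, and discusses adjustment only across arms.

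**Conclusion.** The point holds as a caution on an exploratory analysis. As described, the between-step comparison is confounded by prior suppression, and no stated feature of the plan deals with that. In a same-visit comparison at month 8 the spurious gap is 10 to 30 points on the plan's own correlations, comparable to or larger than the 9%-13% between-arm difference. That result needs only compound symmetry, a constant rate and inert levels.

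Other forms give other answers, including almost no gap or the opposite sign; those results rest on the assumed mixing distribution, and the reversal on pooling also on an assumed rising background rate. The step result therefore cannot be read as evidence about a level unless the analysis form is fixed first. The randomised intent-to-treat comparison is untouched.

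**What to change.** Amend the Aim 1 text as follows.

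1. Report step-specific outcomes descriptively, by visit, and draw no inference about the effect of a level. If a model is used, keep month 4, include visit effects and condition on prior suppression history.
2. For inference on stepping up, add an exploratory comparison by randomised arm of suppression over months 8-24 among participants in both arms who are unsuppressed at month 4. Both arms receive standard care plus automated messaging until then, so this subgroup is defined before care diverges. It estimates the effect of the stepped package, not of a single level.
3. Label any Level 3 contrast that conditions on month 8 as non-randomised, because care has diverged by then.

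The cost is wording and analysis time; viral load is already measured every 4 months in both arms. The downside is a smaller sample: with 80% to 94% unsuppressed at month 4, 88 × .80 = 70 to 88 × .94 = 83 per arm, instead of 88.
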